### Outcomes

The primary outcome is positive symptoms measured on the PANSS-P scale. Secondary outcomes are 1) other psychopathology measures assessed on PANSS negative and general scales; Dimensions of Psychosis Instrument (DIPI) [55]; Clinical Global Impressions - Severity/Improvement/Efficacy (CGI-S/I/E) [56]; Global Assessment of Psychosocial Disability (GAPD) [53]); 2) cognition and cognitive daily functioning measured on Brief Assessment of Cognition in Schizophrenia (BACS) Global Score [57]; Schizophrenia Cognition Rating Scale, Danish version (SCoRS-DK) [58]; Behavioural Rating Inventory of Executive Functions (BRIEF) [59]); 3) HRQoL measured on KIDSCREEN-52 [60]; 4) adverse reactions measured on ‘Udvalget for Kliniske Undersøgelser’ Side Effect Rating Scale (UKU) [61]; Abnormal Involuntary Movement Scale (AIMS) [62]; Simpson Angus Scale (SAS) [63]; Barnes Akathisia Rating Scale (BARS) [64]; cardiac adverse reactions (such as QT-interval prolongation on Electrocardiography (ECG)); somatic events (blood pressure, pulse, body weight, height, body mass index, abdominal circumference, abnormal laboratory test results (fasting blood glucose, insulin and lipid levels, prolactin, other general blood tests)); suicidal ideation measured by K-SADS-PL (specific items); adherence (daily registration by caretakers or staff and antipsychotic blood levels); substance use (interview and urine testing) (Table 1).

**Table 1 T1:** TEA RCT, schedule for outcome assessments during 12 weeks of blinded intervention

**Assessments**	**Inclusion (week 0)**	**Follow-up (week 2)**	**Follow-up (week 4)**	**Follow-up (week 12)**
**Psychopathology and adverse reactions rating scales** PANSS, DIPI, CGI-S, CGI-I, CGI-E, GAPD, UKU, AIMS, SAS, and BARS	X	X	X	X
**Suicidal ideation** K-SADS-PL specific items	X	X	X	X
**Cognition, cognitive daily and executive function** BACS, SCoRS-DK and BRIEF	X			X
**Somatic examination** Standard clinical examination, blood pressure, pulse, weight, height, BMI, and abdominal circumference.	X	X	X	X
**Health-related quality of life** Questionnaire: KIDSCREEN-52	X			X
**Laboratory tests** (see list below)	X		X	X

AIMS = Abnormal Involuntary Movement Scale; BACS = Brief Assessment of Cognition in Schizophrenia; BARS = Barnes Akathisia Rating Scale; BMI = Body Mass Index; BRIEF = Behavioural Rating Inventory of Executive Functions; CGI = Clinical Global Impression (-I = Improvement -S = Severity -E = Efficacy); DIPI = Dimensions of Psychosis Instrument; GAPD = Global Assessment of Psychosocial Disability; HRQoL = Health related quality of life; K-SADS-PL = Kiddie-SADS-Present and Lifetime Version; KIDSCREEN-52 = Health related quality of life questionnaire for children and young people and their parents; PANSS = Positive and Negative Syndrome Scale; SCoRS-DK = Schizophrenia Cognition Rating Scale – Danish version; UKU = ‘Udvalget for Kliniske Undersøgelser’ Side Effect Rating Scale.

Laboratory tests: Blood tests (fasting): triglycerides; total cholesterol; high-density and low-density lipoproteins; glucose; insulin; prolactin; creatinphosphokinase; haemoglobin; leukocyte cell and differential count; thrombocyte cell count; sodium; potassium; creatinine; aspartate amino transferase; alkaline phosphatases; thyroid stimulating hormone; vitamin D; omega 3 fatty acids; genetic material (DNA). Blood samples to analyse serum values of antipsychotics are drawn at week 4 and 12, and saved for later analysis. Urine tests: pregnancy test (at baseline and at follow-up if suspicion of pregnancy), screening for medication and substance abuse (at baseline and at follow-up if suspicion of substance use). ECG: Standard leads.

### Antipsychotic drugs

#### **
*Quetiapine and aripiprazole*
**

Quetiapine is a low-affinity dopamine D2 receptor antagonist [65]. Aripiprazole has a high affinity for dopamine D2 receptors but with a partial agonist mode of action at this receptor [66]. Both compounds are approved by FDA and the European Medicines Agency (EMA) for the treatment of schizophrenia in adults. Aripiprazole is approved by the FDA for use in schizophrenia for ages 13-17 years, and in Denmark and the rest of the EU it has obtained authorisation for use in adolescent schizophrenia for ages of 15-17 years by the EMA [67]. Quetiapine has FDA approval for the treatment of schizophrenia for ages 13-17 years, but it has not been approved by EMA for use below age 18 years. In the present trial, quetiapine and aripiprazole were selected since these compounds are frequently used in clinical child and adolescent psychiatric practice, and because it remains unclear whether their different receptor binding profiles can be related to differences in clinical outcomes in EOP. In adults, a recent Cochrane systematic review found no significant differences between quetiapine vs aripiprazole (global state (n = 991, 12 RCTs); PANSS-P (n = 583, 7 RCTs); leaving the study early for any reason (n = 168, 2 RCTs), or general extra pyramidal symptoms (n = 348, 4 RCTs); all low to very low quality evidence). Results were significantly in favor of aripiprazole regarding Quality of Life (n = 100, 1 RCT, mean difference 2.60, 95% CI 1.31 to 3.89), however, evidence was rated very low quality [51]. Notably, all studies were conducted in China and in adult Chinese patients. Currently, no single Western RCT has compared quetiapine with aripiprazole either in adults or in children and adolescents.

#### **
*Quetiapine and quetiapine extended release*
**

Studies have shown that quetiapine 200-800 mg/day improves psychotic symptoms in patients with EOP (age 11-17 years) [68], and 300-800 mg/day showed acceptable long-term (88 weeks) safety and tolerability (n = 10, age 12-16 years [69]). Patients aged 10–17 years (n = 27) tolerated quetiapine doses of 400 mg twice daily, with no serious AEs and no unexpected events reported, and compared to a parallel adult population there were similar pharmacokinetic, safety, and tolerability profiles by dose escalation, suggesting that no dosage adjustment is required when treating patients of these ages [70]. One 6-week, double-blind, placebo-controlled RCT of quetiapine 400 or 800 mg/day in 220 adolescents with schizophrenia aged 13-17 years found significant improvements in PANSS total score changes at both quetiapine doses compared with placebo, and quetiapine was generally well tolerated with a profile broadly similar to that reported in adult populations [15]. A 12-week open label study of quetiapine in 56 adolescents with schizophrenia spectrum disorder found a significant reduction of PANSS total and particularly positive symptom scores [71]. It is generally assumed that younger patients require lower doses of antipsychotics than adults. However, for quetiapine this may be true for younger children with lower body weight, but adolescents typically require rapid titration to the same, or even higher, dose levels than adults for optimal clinical response [32]. Higher doses of quetiapine than those recommended by the compound producer have proven to be effective and safe in adolescents [26]. Extended release quetiapine allows a once-daily dosing and has been proven effective and well tolerated in adults with schizophrenia in a randomised, placebo-controlled trial [72]. This formulation will be used in the present trial in order to match the once a day dosing of aripiprazole.

We use a 9-day fixed titration phase with a final quetiapine extended release dose of 600 mg/day (Table 2). If needed for efficacy, the possible maximum dose can be titrated up to 800 mg/day, or titrated down to a lower dose level if not tolerated (minimum 50 mg/day).

**Table 2 T2:** Schedule of dosing regimen

**Level**	**1**		**2**		**3**		**4**		**5***	**6****
**Day**	**1**	**2**	**3**	**4**	**5**	**6**	**7**	**8**	**9**	**…**
**Quetiapine ER (mg)**	50	50	100	100	200	200	400	400	600	800
**Aripiprazole (mg)**	2.5	2.5	5	5	10	10	15	15	20	30
**Number of capsules**	1	1	2	2	1	1	2	2	3	4
**Quetiapine ER:**	**●**	**●**	**●●**	**●●**	**●**	**●**	**●●**	**●●**	**●●●**	**●●●●**
**Aripiprazole:**	**●**	**●**	**●○**	**●○**	**●**	**●**	**●○**	**●○**	**●●○**	**●●○○**

Due to unparalleled strengths in formulations of quetiapine ER and aripiprazole, the use of capsules filled with a neutral ingredient (lactose) is needed in order to have the same number of capsules for each compound at each level. ER=extended release.

*Level 5 = final level; **Level 6 = maximal level (if needed);

**●**Capsules with active compound; **○** Capsules without active compound.

#### **
*Aripiprazole*
**

The safety of aripiprazole used in children and adolescents from the age of 7 years has mainly been documented in open-label or naturalistic studies of disorders other than psychosis, i.e., Tourette’s syndrome or developmental disorders, using doses in the mean range of 5-17 mg/day [73-78]. A double-blinded multi-centre RCT compared aripiprazole 10 mg/day and 30 mg/day with placebo in 302 adolescents (aged 13-17 years) with schizophrenia [11]. The trial authors concluded that 6 weeks treatment with aripiprazole was generally well tolerated and lead to significant improvements in psychotic symptoms compared with placebo. An open-label trial with 21 patients aged 10-17 with bipolar or schizophrenia spectrum disorders compared daily doses of 20, 25 or 30 mg aripiprazole in a 12-days titration phase, followed by a 14-days fixed dose phase. Effectiveness and criteria for tolerability were met for all doses, and no adverse reactions met the regulatory criteria for serious adverse reactions [79].

We use a 9-day fixed titration phase with a final aripiprazole dose of 20 mg/day (Table 2). If needed for efficacy, the possible maximum dose can be titrated up to 30 mg/day. If final doses are not tolerated, patients can be titrated down to a lower dose level (minimum 2.5 mg/day).

#### **
*Concomitant medications*
**

Patients will not be allowed any concomitant antipsychotic medication before all trial assessments at week 12 have been conducted. Concomitant medication of any kind beyond trial medications will be recorded throughout the trial intervention period.

### Sample size estimation

The sample size estimation is based on the primary outcome measure, the PANSS-P score. In 2009, when the TEA trial was designed, the estimated standard deviation (SD) for PANSS-P was based on the few studies that up until then had investigated efficacy of the trial drugs (quetiapine or aripiprazole) in patients below 18 years of age with psychosis [11,20,71]. The three studies reported mean PANSS-P in patients treated with quetiapine or aripiprazole with SDs ranging from 4.1 to 7.4, or standard error (SE) for change of PANSS-P from entry to end of treatment of around 0.6 (corresponding to SD = 5.9). Furthermore, in our previous case-control study of patients comparable to the TEA participants, consisting of Danish minimally medicated children and adolescents with psychosis aged 12-18 years, the SD of PANSS-P at the time of first-episode psychosis was within the above range, SD = 5.1 [80,81]. Consequently, we used a conservative estimate of the (at that time) highest reported SD of 7.4 in the original sample size estimation. Since then, however, more studies on aripiprazole and quetiapine in early onset psychosis point toward lower SDs on the PANSS-P ranging from 4.3 to 6.3 [15,21,28] (see all relevant studies in Table 3). A weighted mean SD of PANSS-P based on data from all 6 studies in Table 3 equals 5.48 for all SDs, and 5.68 for SDs of change scores. Hence, based on the entirety of the available data, we updated our sample size calculation based on a SD of 5.7 on the PANSS-P scale.

**Table 3 T3:** Data from trials on quetiapine or aripiprazole in patients below 19 years with psychosis used for final power calculation

**Study (reference)**	**Design and population**	**Intervention**	**ITT population N**	**PANSS-P scores baseline (SD)**	**PANSS-P scores follow-up (SD)**	**Change PANSS-P scores from baseline to follow-up (SD)**
Schimmelman et al. 2007 [71]	Open Label	Quetiapine	N=52	Quetiapine:	Quetiapine:	Quetiapine:
	Non-RCT					
	12 weeks	200-800 mg		21.4 (5.2)	14.5 (7.4)	-6.9 (na)
	Schiz. spectrum					
	Most drug-naïve					
	12-17 years					
Findling et al. 2008 [11]	Double-blind RCT 6 weeks	Aripiprazole 10 mg/30 mg vs placebo	N=302 (100 vs 100 vs 102)	Aripiprazole 10 mg: 22.1 (SD=5.0)	Aripiprazole 10 mg: 14.5 (SE=0.6 i.e. SD=6.0*)	Aripiprazole 10 mg: -7.6 (SE=0.6 i.e. SD=6.0*)
	Schiz. 13-17 years					
				Aripiprazole 20 mg: 23.5 (SD=5.0)	Aripiprazole 20 mg: 15.4 (SE=0.6 i.e. SD=5.9*)	Aripiprazole 20 mg: -8.1 (SE=0.6 i.e. SD=5.9*)
Arango et al. 2009 [20]	Open label RCT	Quetiapine vs Olanzapine	N=50	Quetiapine:	Quetiapine:	Quetiapine:
	6 months		(24 vs 26)	23.3 (7.3)	15.1 (4.1)	-8.2 (na)
	Psychotic disorders					
	Most drug-naïve	flexible doses				
	12-18 years					
Swadi et al. 2010 [21]	Open label RCT	Quetiapine up to 800 mg vs risperidone up to 6 mg	N=22	na	na	Quetiapine:
	6 weeks		(11 vs 11)			-9.6 (5.5)
	First episode					
	psychosis					
	Below 19 years					
Findling et al. 2012 [15]	Double-blind RCT	Quetiapine 400 mg/800 mg vs placebo	N=220 (73 vs 74 vs 73)	Quetiapine 400 mg: 23.3 (5.8) Quetiapine 800 mg: 23.8 (4.8)	na	Quetiapine 400 mg:
	6 weeks Schiz.					-8.6 (SE 0.7, i.e. SD=6.3*)
	13-17 years					Quetiapine 800 mg:
						-9.3 (SE 0.6, i.e. SD=5.1*)
NCT01009047 2013 [28]	Double-blind RCT	Paliperidone ER 3-9 mg vs Aripiprazole 5-15 mg	N=226 (112 vs 114)	Aripiprazole: 22.5 (4.3)	na	Aripiprazole week 8:
	8 weeks/26 weeks					-6.2 (4.9)
	Schiz.					Aripiprazole week 26:
	12-17 years					-8.3 (6.1)

Data on PANSS positive scores and standard deviations from these studies were considered in the sample size estimation of the TEA study. Weighted average of all SDs=5.48 and of change in SD=5.68. ITT=Intention-to-treat. PANNS-P=Positive and Negative Syndrome Scale – positive score. SD=standard deviation. SE=standard error. na=not available. ER=extended release formulation. vs=versus. Schiz.=Schizophrenia. *SD=SE√n.

Based on results from a 24 weeks RCT comparing olanzapine with quetiapine that found a mean difference in PANNS-P scores of 4 points in favour of olanzapine (a difference that did not reach significance probably due to the small group size of 25 patients each) [20], we decided that a minimal clinically relevant difference between outcome responses of quetiapine vs aripiprazole after (the shorter period of) 12 weeks of treatment would be 3 points on the PANSS-P. Hence, using a power of 80% and a two-sided alpha of 5%, and expecting a SD of 5.7 on the PANSS-P, the required sample size necessary to detect or reject a difference of at least 3 points on PANSS-P was estimated as follows (N = total sample size, SD of the primary outcome measure = 5.7 (we assume SD_1_ = SD_2_), α = type 1 error = 0.05, β = type 2 error = 0.20, MIREDIF = minimal relevant difference of outcome measure = 3, z = fractiles in normal distribution): *N = 2 * (SD*_*1*_^*2*^ *+ SD*_*2*_^*2*^*) * (z*_α*/2*_ *+ z*_β_*)/MIREDIF*^*2*^ *= 112.* Accordingly, we should strive to include a total of 112 patients, equivalent to about 56 patients in each of the intervention groups.

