### Post-randomisation exclusions

Patients are excluded if there is a significant worsening of their clinical state during the course of the trial (i.e., increases of 20% or more from baseline on the PANSS total score).

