### Sample size estimation

The key consideration in designing a RCT is to know the size of a sample needed to obtain limited probability of type 1 (false positive) and type 2 (false negative) errors. The sample size estimation is based on choices regarding an acceptable risk of type 1 and 2 errors, on assumptions regarding the variation in outcome measures, and finally on the estimation of the minimal relevant difference in clinical effect between the interventions under the trial. Thus, the following four variables were considered:

1) α or type 1 error (the probability of rejecting the null hypothesis when it is actually true) is usually set at 0.05 two-sided. If we find a difference below this level we may declare a significant difference, knowing that there will still be a 5% risk that the null hypothesis of no difference is correct.

2) We decided in our updated sample size estimation to use a value of 80% for power, which is standard and translates into accepting a 20% risk that we will miss a true difference of the anticipated magnitude between the two compounds of (in this case) 3 points on the PANSS-P scale.

3) The expected variation in the primary outcome measure PANSS-P was initially driven by the only three relevant RCTs (upper three studies in Table 3) that were available in 2009 [11,20,71]. During our recruitment in the TEA trial, more informative studies have appeared (lower three studies in Table 3), i.e., two published RCTs [15,21] and one RCT reported to clinicaltrials.gov [28]. Based on a weighted mean SD of change in PANSS-P scores from all six trials, we used in our updated sample size calculation a SD of 5.7 on the PANSS-P scale.

4) MIREDIF should represent a meaningful minimal difference in response in the sense that it would justify a choice between two interventions in a clinical setting. The PANSS-P scale scores range from 7 to 49, and the few relevant RCTs already conducted found that the mean PANSS-P score after 6 weeks to 6 months of treatment is around 15 in the aripiprazole or quetiapine groups with a mean PANSS-P score change in the range 6.2–9.6. For the TEA trial, we decided in our updated sample size estimation, based on data from a head-to-head trial comparing olanzapine vs quetiapine in EOS [20], that it would be clinically relevant to be able to detect a difference of 3 points in outcome score on the PANSS-P scale between the two drugs.

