The original and the updated TEA calculations and examples of different values of MERIDIF (minimally relevant difference), SD (standard deviation) and β (risk of type II error) are shown. As can be seen, the larger the MIREDIF you wish/expect to be able to detect or the smaller the estimated SD of the outcome measures or the larger the β, the smaller the sample size needed. In these calculations we used a two-sided α (risk of type I error) = 0.05 and we assumed SD_1_ = SD_2_. Effects sizes depend on MIREDIF and SD. Compared to the original calculation, the updated sample size calculation is balanced by allowing for a larger β, expecting a zsmaller SD and lowering the detectable MIREDIF. z = fractiles in normal distribution. ^#^N = 2 * (SD_1_ ^2^ + SD_2_ ^2^) * (z_α/2_ + z_β_)/MIREDIF^2^ ⇒ N = 4 * (z_α/2_ + z_β_)^2^ * (SD_1_/MIREDIF)^2^. The product 4 * (z_α/2_ + z_β_)^2^ is rounded up to whole figures in the equations.

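### The 112 patients give about 80% power only if all of them contribute week-12 data; no allowance is made for loss, and the printed formula and rounding note are wrong.

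*Protocol article*

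**What the plan says.** Methods/Design, Sample size estimation, gives the inputs: "using a power of 80% and a two-sided alpha of 5" per cent, "expecting a SD of 5.7 on the PANSS-P", and a relevant difference that "would be 3 points on the PANSS-P". It prints a formula, states the result as 112, and concludes: "Accordingly, we should strive to include a total of 112 patients, equivalent to about 56 patients in each of the intervention groups". The Discussion repeats the decision "to use a value of 80% for power" and reports that all 112 patients have been included.

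The footnote to Table 4 prints the general formula with the term "z_α/2_ + z_β_)/MIREDIF^2", that is, with no square on the sum of the two normal fractiles, and then says that it implies a second form in which the sum is squared. It adds that the product 4 × (z_α/2 + z_β)² "is rounded up to whole figures in the equations".

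On loss of data, Post-randomisation exclusions says "Patients are excluded if there is a significant worsening of their clinical state", defined as a rise of at least 20% in PANSS total. Data analysis names a modified intention-to-treat analysis and multiple imputation where missingness calls for it. No dropout rate or inflation factor appears anywhere. Strengths and limitations names a larger SD than expected as the threat to power for the primary outcome and does not mention attrition.

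**The concern.** A sample size formula returns the number of patients who must be analysed. Here that number is also the number randomised, in a 12-week trial of adolescents with psychosis whose own text provides for exclusions and missing outcomes. The nominal power had already been lowered from 90% to 80% in the updated calculation, so no reserve remains.

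The Methods present 112 as enough either to find or to rule out a 3-point difference. If the information at week 12 comes from fewer patients, a non-significant result supports that conclusion less well than a reader of the 80% figure would think.

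The formula and rounding errors matter for a different reason. A reader who checks the Methods equation cannot reach 112 from it, and the footnote describes a rounding that was not done.

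**Working it through.** **Inputs from the article.** α = 0.05 two-sided (z = 1.960); power 80% (z = 0.842); SD 5.7 in both arms; difference 3; 1:1 allocation with about 56 per arm.

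**1. Reproducing 112.** Table 4 uses N = 31 × (5.7/3.0)² = 31 × 3.61 = 111.9, giving 112. The figure reproduces.

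**2. The multiplier.** 4 × (1.960 + 0.842)² = 31.40 at 80% power. The corresponding value at 90% power (z = 1.282) is 42.03. Table 4 uses 31 and 42, so both were rounded down, contrary to the footnote.

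| Multiplier | N = multiplier × 3.61 | Total in equal arms |
|---|---|---|
| 31 (used) | 111.9 | 112 |
| 31.40 (exact) | 113.3 | 114 |
| 32 (rounded up, as stated) | 115.5 | 116 |

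**3. The formula as printed.** Without the square: 2 × (5.7² + 5.7²) × (1.960 + 0.842) / 3² = 129.96 × 2.802 / 9 ≈ 40. The squared form in the Table 4 header gives the 112, so the omission has no effect on N.

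**4. Power with all 112 analysed.** Standardised difference: 3 / (5.7 × √(2/56)) = 2.785. Normal approximation: Φ(2.785 − 1.960) = 79.5%. Noncentral t with 110 degrees of freedom: 78.8%. With 57 per arm the figures are 80.2% and 79.5%; the t-test first passes 80% at 58 per arm (80.2%).

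**5. Power with loss.** The loss rates are assumptions, since the article gives none. The calculation is an unadjusted two-sample t-test on completers, SD 5.7, difference 3.

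| Assumed loss | Analysed | Power (t) |
|---|---|---|
| 0% | 112 | 78.8% |
| 10% | 101 | 74.5% |
| 20% | 90 | 69.5% |

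**6. Possible offset.** If covariates correlate r with the analysed outcome, the residual SD is 5.7 × √(1 − r²). By the normal formula with assumed r:

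| Assumed r | Residual SD | No loss | 10% loss | 20% loss |
|---|---|---|---|---|
| 0.3 | 5.44 | 83.1% | 79.1% | 74.3% |
| 0.5 | 4.94 | 89.5% | 86.2% | 82.0% |

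The article gives no r. Its SD of 5.7 comes from change scores, and the stratification variables to be adjusted for are a two-level PANSS-P score and a two-level age group, so r cannot be inferred from the text.

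**The case against.** The strongest reply is that 112 reproduces. By the article's own normal-theory method, power is 79.5% with all patients analysed, half a point short of the target. A gap of two to four patients is immaterial when the text speaks of about 56 per arm. This stands: the rounding alone is no reason to call the trial underpowered.

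It is also fair that the completer t-test is not the planned analysis. Data analysis provides for adjustment for the stratification variables, possible further covariates, use of the repeated assessments and multiple imputation. PANSS is measured at weeks 2 and 4, so patients lost before week 12 can still contribute. The figures under loss are therefore illustrations, not estimates of the trial's power. However, the sample size calculation takes no credit for these features, and imputation does not restore all the information that is lost.

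The article does not say whether patients who worsen are excluded from treatment or from the analysis set, so that rule cannot be counted as a known loss of outcomes. A separate paper is to give the detailed analysis plan, but that does not settle a calculation that the article sets out in full.

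A reader might infer from the printed formula that the true requirement is 40, or that the misprint lowers power. Neither follows, because Table 4 uses the squared form in every row. A reader might also take the abstract to claim 80% power. It says only that 112 rests on a sample size estimation.

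**Conclusion.** The point holds in conditional form. At SD 5.7 and a 3-point difference, 112 patients give 79.5% power (normal) or 78.8% (t-test) if every patient contributes week-12 data, and less otherwise. The article states 80% without that condition, makes no allowance for loss and omits attrition from its discussion of power.

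The size of any shortfall depends on figures the article does not give. Assumed losses of 10% and 20% lead to about 75% and 69% in an unadjusted completer comparison, and the planned analysis may recover part of that.

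A reader might conclude that the trial as run has clearly less than 80% power. The article does not support this: it reports no attrition, and the last patients were still finishing blinded treatment when it was written.

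The missing square and the rounding statement are plain errors in the text. The first has no effect on N. The second accounts for two patients against the exact value, or four against the rounding as described.

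**What to change.** No further enrolment is needed. Four text changes are enough:

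1. Put the square on (z_α/2 + z_β) in the Methods equation and in the Table 4 footnote.
2. Either say that the multiplier is rounded to the nearest whole figure, which leaves Table 4 as it stands, or use 31.4 and give the required total as 114.
3. State the power conditionally, for example: 112 patients give about 79% power for a 3-point difference at SD 5.7 if all contribute week-12 data, and less with loss; in an unadjusted completer t-test, about 75% at an assumed 10% loss and 69% at 20%, part of which the planned adjustment and repeated assessments may recover.
4. Name attrition beside the larger SD in Strengths and limitations as a threat to power for the primary outcome.

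The cost is a text correction and a slightly less favourable power statement. The design, the number of patients and the analysis do not change.
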